### Enrolment

Patients will be recruited based on primary MRI by the local multidisciplinary team (MDT) during an MDT meeting. The imaging of possibly eligible patients will be discussed in a monthly central meeting with the study team and local investigators from other study sites or anonymously in a coded and secured app (Siilo from Doctolib). When eligibility is confirmed, all patients will be required to provide written informed consent (online supplemental file A).

### MRI assessment by trained radiologists

Primary MRI scans are evaluated by the local radiologists and assessed according to online supplemental file B. These radiologists have completed an interactive training provided by expert radiologists from the LaNoReC study group, where the lateral compartments are discussed with specific attention to classifying the anatomical location and accurate measurements of LLNs.^14^ During the study, local radiologists will have access to two visual atlases illustrating the lateral compartments and an instruction manual to reassure the accurate diagnostics and uniform reporting of LLNs. Additional imaging will be performed according to local guidelines. For inclusion in this study, a restaging MRI after neoadjuvant treatment is advised; however, treatment decisions should be based on the primary LLN size. A restaging MRI is not obligatory but is already a standard practice in many centres. A follow-up MRI 2 years postoperatively is advised for the detection of LLR.

### Neoadjuvant radiotherapy delineation by trained radiation oncologists

Radiotherapy will take place by radiation oncologists who have completed training regarding the delineations of the lateral compartments. The delineations of the lateral compartments of the first three included patients from each centre will be evaluated by an expert radiation oncologist from the LaNoReC study team to ensure adequate coverage. Delineation of the lateral compartment and visible lymph nodes should be performed according to the renewed Dutch association of radiotion oncologists guideline (Landelijk Platform Radiotherapie Gastro-Entrerologische tumoren (LPRGE), (online supplemental file C)) to ensure adequate coverage of the lateral compartments.

In accordance with the registration design of this study, patients will undergo neoadjuvant therapy schedules according to local guidelines decided by their multidisciplinary team.^25^ These neoadjuvant options include (C)RT or total neoadjuvant treatment regimens including radiotherapy such as RAPIDO (the Rectal cancer And Preoperative Induction therapy followed by Dedicated Operation), which consists of short course radiotherapy followed by six courses of systemic chemotherapy^26^, or systemic chemotherapy combined with CRT. Based on the most recent literature, it is not recommended to give LLNs an additional irradiation boost due to limited oncological advantages and increased risks.^21^ Nevertheless, boosting of LLNs is allowed as part of the study treatment.

### Nerve-sparing LLND procedure by trained surgeons

LLNDs will only be performed by a select team of surgeons after completing adequate human cadaver training, intensive proctoring and assessment of procedural videos. Only surgeons who participated in this training can be nominated with their hospital to act as referral centre or the surgeons can be invited to perform the resection in the (local) referring centre. All ‘study-LLND’ procedure videos will be discussed during monthly meetings for quality control.

Patients with primarily enlarged (≥7.0 mm SA) LLNs are advised to undergo an LLND. Moreover, LLND should be considered in patients with an intermediate (5.0–6.9 mm SA) LLN with at least one malignant feature. LLNDs should be performed according to a minimally-invasive, nerve-sparing technique. If preoperative MRI shows the lateral extension of the tumour into the nerve plexus or an exenteration is required, the patient will still be included to analyse oncological and functional outcomes; however, the patient is not included in the main analyses (see sample size section). If in a shared decision-making process, the patients decide not to undergo an LLND, they remain in the study and are followed for collection of oncological outcomes. In case of a complete clinical response of the tumour and shrinkage of the LLN(s), a patient may enter a watch-and-wait protocol; in these cases, patients should be closely monitored and an LLND may be omitted.

The surgical technique for LLNS has been previously described in detail.^24^ The procedure involves the excision of all lateral lymphatic tissues within the internal iliac and obturator compartment along three anatomical planes: (1) the medial plane defined by the ureter and pelvic plexus (ureterohypogastric fascia), (2) the lateral plane bounded by the psoas and internal obturator muscle and (3) the dorsal plane defined by the internal iliac vessels and the sciatic nerve. It is important to note that the lymphatic tissue along the external iliac arteria is not dissected during this procedure.

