### Sample size

The sample size is based on a historical control group with an average 3-year LLR rate of 13% (11% Snapshot and 16% Consortium) in low LARC with LLNs ≥7.0 mm after (C)RT+TME (without LLND), which is the current standard treatment in Europe.^5 6 14^ It is hypothesised that (C)RT+TME+LLND can reduce this rate to 6%, as found by the Consortium study. A one-group χ^2^ test with a 5% two-sided significance level will have 90% power to detect the difference between the null hypothesis proportion of 0.13 and the alternative proportion of 0.06 when the sample size is 190. If correcting for a drop-out rate of 5%, 200 patients are needed. Included patients in need of more extensive surgery (ie, pelvic exenteration or presumed inability to spare the hypogastric nerves on MRI) will be registered and analysed as a separate cohort since these more extensive tumours have higher LLR rates and cannot undergo nerve-sparing LLND.

Annually, approximately 882 patients present with low LARC and are treated with neoadjuvant therapy in the Netherlands.^14^ Considering 122 (14%) of these patients have LLNs ≥7.0 mm, a minimum 2.5-year inclusion period is needed to achieve the estimated sample size (expecting 60% of eligible patients to be enrolled).^14^ As some of the eligible patients will undergo open surgery, it is expected that the inclusion period may require an extension. An interim analysis will be carried out after the inclusion of the first 75 participants. The goal of this interim analysis is to evaluate early indicators of effectiveness concerning oncological outcomes, particularly LLR rate, and to evaluate safety by examining short-term surgical complications (within 90 days) and early functional outcomes (urogenital dysfunction within 3 months). The results will help improve the preoperative information provided to patients. If the interim analysis reveals a high LLR rate that suggests that the hypothesis may not be achievable or significant morbidity within 3 months of surgery, the study team will consider to prompt the study ahead of time.

Additionally, patients with rectal cancer and an LLN of 5.0–6.9 mm SA with at least one malignant feature will be investigated. For this analysis, a sample size calculation is impossible due to limited data. Therefore, all eligible patients in this group will be collected during the study period.

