The inclusion criteria for the LaNoReC study are based on the Snapshot and the Consortium study, in which the combination of (C)RT and TME was insufficient for adequate treatment of patients with enlarged LLNs.^5 14^ Besides short-axis size, the recurrence rates seem to be also influenced by other radiological criteria, such as the presence of malignant features which increased the LLR rate in intermediate LLNs to 8% (vs 2% in absence of malignant features). In enlarged nodes, the presence of two or more malignant features was associated with an increased LLR rate of 17% after 4 years, while no LLR developed if such features were absent. Since the influence of malignant features has only been described in small subgroups and should be interpreted with caution, the inclusion criteria and LLND recommendations for the LaNoReC study are based on short-axis size only for enlarged nodes and intermediate nodes specifically combined with the presence of malignant features. By including this intermediate node group, the LaNoReC study aims to dissolve the current lack of knowledge regarding treatment options and oncological outcomes in those patients. After thorough evaluation during multidisciplinary meetings and a shared decision-making process with the patient, an LLND can be considered to lower the LLR rate.

The inclusion criteria described in the previous paragraph should be based on primary MRI, as the Consortium study is the only study which found that sufficient downstaging on restaging MRI (shrinkage of iliac and obturator LLNs to ≤4 mm and ≤6 mm, respectively) could avoid LLND.^5^ The Snapshot study, however, showed that downsizing of LLNs below the Consortium cut-offs still resulted in an unacceptably high LLR rate of up to 15%.^14^ The inclusion criteria for the LaNoReC study are based on the results of the Snapshot study because of the high validity of these findings due to the training of radiologists. Exempted from this are those with a complete clinical response for which a watch-and-wait trajectory is increasingly applied. Although these patients were not included in the Snapshot study, and therefore restaging results are not applicable to this group, we believe an LLND can be omitted in these cases and close surveillance is justified.

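### The rule that places patients in the separate extensive-surgery cohort is worded in two ways and given no assessment time, so an enrolled patient can leave the main analysis after neoadjuvant treatment has begun

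*Protocol article*

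**What the plan says.** Study population and Enrolment in the protocol article base eligibility and recruitment on the primary MRI. The Discussion repeats this for node size: "The inclusion criteria described in the previous paragraph should be based on primary MRI".

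The rule for leaving the main analysis appears twice.

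- Nerve-sparing LLND procedure by trained surgeons: "If preoperative MRI shows the lateral extension of the tumour into the nerve plexus or an exenteration is required", the patient stays in the study but not in the main analyses. The text then points to the sample size section.
- Sample size: "Included patients in need of more extensive surgery (ie, pelvic exenteration or presumed inability to spare the hypogastric nerves on MRI") form a separate cohort. The reasons given are that these tumours carry a higher LLR rate and cannot have a nerve-sparing LLND.

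On imaging, MRI assessment by trained radiologists advises a scan after neoadjuvant treatment without requiring it: "A restaging MRI is not obligatory but is already a standard practice in many centres". Table 1 lists that scan after (C)RT, marked as not required.

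The Introduction and Study design count radiotherapy by trained radiation oncologists as part of the optimised care being evaluated. The Statistics section compares LLR with 13% by a one-sample z-test.

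**The concern.** The rule decides who is counted in the primary test, and two things about it are unsettled.

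**Wording.** One section asks for an imaging finding, namely tumour reaching the nerve plexus. The other asks for a judgement, namely that the hypogastric nerves probably cannot be spared. The two agree on exenteration, but two readers could classify the same scan differently.

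**Timing.** Eligibility is tied to the primary MRI; this rule is not. A scan after (C)RT is also preoperative, and the exenteration limb has no date at all. As written, a patient can enter the main cohort, receive radiotherapy, and then be moved out on what is seen afterwards. Because the later scan is optional, the opportunity for MRI-based late moves also differs between centres.

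In a single-arm comparison with a fixed rate, taking out enrolled patients at higher risk after the tested treatment has started can lower the observed LLR without the package having done better. A result near the significance limit could then depend on when the cohort was assigned.

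**Working it through.** **1. The plan's own figure.** The inputs are from Sample size: "the null hypothesis proportion of 0.13 and the alternative proportion of 0.06 when the sample size is 190", and "5% two-sided significance level will have 90% power".

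n = [(1.960·√(0.13·0.87) + 1.282·√(0.06·0.94)) / 0.07]² = 189.5, rounded up to 190. With 5% drop-out, 190/0.95 = 200. Both stated figures are reproduced and are not in dispute.

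**2. The significance limit at n = 190.** Using the z-test with null variance, two-sided 5%, the standard error is √(0.13·0.87/190) = 0.0244.

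- 15 events: 7.9%, z = (0.0789 − 0.13)/0.0244 = −2.09, p = 0.036.
- 16 events: 8.4%, z = (0.0842 − 0.13)/0.0244 = −1.88, p = 0.061.

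So 15 events are significant and 16 are not.

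**3. What late removal could do if the package meets its target (illustration).** The documents give neither the share of patients moved late (m of 190) nor their LLR (r); both are assumptions. The 6% in all other patients is the protocol's target. If the late movers are removed, the rate is 6.0%. If they are kept, it is [(190 − m)·0.06 + m·r]/190:

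| Moved late | Assumed LLR | Expected events | LLR if kept | At the expected rate |
|---|---|---|---|---|
| 10 (about 5%) | 30% | 10.80 + 3.00 = 13.80 | 7.3% | significant |
| 19 (10%) | 20% | 10.26 + 3.80 = 14.06 | 7.4% | significant |
| 19 (10%) | 30% | 10.26 + 5.70 = 15.96 | 8.4% | not significant |
| 19 (10%) | 40% | 10.26 + 7.60 = 17.86 | 9.4% | not significant |

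**4. What it could do if the package has no effect (illustration).** Suppose all enrolled patients have 13%, a share e with LLR r leaves, and 190 remain for analysis. The remaining rate is (0.13 − e·r)/(1 − e). With no removal, the binomial probability of 15 or fewer events is 1.9%. With e = 10%:

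- r = 20%: remaining rate 12.2%, probability 3.8%.
- r = 30%: remaining rate 11.1%, probability 9.3%.
- r = 40%: remaining rate 10.0%, probability 20%.

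These figures hold only if the cohorts behind the 13% kept such patients, which the documents do not say.

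**5. The cost of keeping late movers.** In the 10%/30% case of step 3, the probability of 15 or fewer events among 190 falls from 89% (all at 6%) to about 46%.

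**The case against.** The strongest reply is that this is one rule with a short cross-reference. The surgical section defers to Sample size, both name exenteration, and both concern nerves that cannot be spared. The primary MRI is the only required preoperative pelvic MRI, the removed patients are still followed and reported, and a condensed article may leave the assessment date to the full protocol. The flowchart in Figure 1 is not available to check.

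Much of this stands, and it rules out several stronger readings.

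- A reader might infer that the protocol uses the restaging MRI to drop poor responders. No section says so; the text leaves it possible.
- A reader might infer that a large lateral node lying against the nerves stays in under one wording and leaves under the other. Sample size explains its rule by the extent of the tumour, which undercuts that example.
- A reader might take the Discussion's insistence on the primary MRI as contradicting the rule. That paragraph is about node size and downsizing, not plexus involvement or exenteration.
- A reader might infer a demonstrated bias towards success. That requires the historical cohorts to have kept comparable patients. The benchmark is described as a rate after (C)RT and TME, and the documents are silent on a matching exclusion. If later scans count, patients whose tumours regress could also move into the main cohort.

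What the reply does not remove is the text itself. It names no scan and gives the exenteration limb no date, although the article specifies the primary MRI for eligibility. That is a loosely fixed boundary of the primary analysis set, not merely an omitted detail.

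**Conclusion.** The point holds as a problem of definition and timing. Two sections give different MRI criteria for one cohort, and neither ties the decision to a time before treatment. Followed as written, the rule lets enrolled patients, described by the protocol as having higher LLR, leave the primary test after the tested radiotherapy has begun.

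The likely direction is a lower observed LLR, but the size cannot be computed from the documents. It rests on three unknowns: the share moved late, their LLR, and whether the 13% carries the same exclusion. The assumed 10%/30% case sits almost exactly on the 15/16-event limit, and two of the four scenarios in the table remain significant, so the arithmetic shows only that the choice can matter. Having a separate cohort for extensive surgery is legitimate, and the sample size calculation is correct. This is an inexpensive improvement worth making, not a fatal flaw.

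**What to change.** 1. Reconcile the surgical and Sample size sections into a single criterion for the separate cohort. Which clinical criterion to use is for the study team to decide.
2. Assign the cohort once, from the primary MRI, when eligibility is confirmed at the central meeting or in the app, and record it in Castor before neoadjuvant treatment starts.
3. Keep patients assigned to the main cohort in the main analysis if the operation later changes.
4. Report how many such changes occurred, and give the LLR without those patients as a sensitivity analysis.

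This alters cohort assignment only; nobody's treatment changes. The practical cost is an edit to two sections and one database field. The statistical cost is that some patients without a nerve-sparing LLND stay in the main analysis, so the observed LLR may be less favourable and power lower if late changes are common. Keeping later exenterations in a comparison with a (C)RT and TME rate may also introduce a mismatch of its own, which is why the sensitivity analysis should be reported alongside.

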### Evaluation of the resection specimen by trained pathologists and grossing assistants

To ensure adequate assessment of resection specimens, pathologists in each participating centre received a protocol (online supplemental file D) to ensure that LLND specimens are adequately and uniformly examined. This protocol was developed by expert pathologists from the LaNoReC study team with experience regarding the assessment of LLND specimens.

### Follow-up and questionnaires

Patients undergo standard oncological follow-up for at least 36 months. At 24 months, a pelvic MRI is advised to evaluate early LLR (see table 1). This MRI will also be reviewed by the participating radiologist. The EORTC-C30, EORTC-CR29, EQ-5D and LARS questionnaires are distributed before surgery and at 6 months, 12 months and 36 months after surgery (table 1). The LARS questionnaire will not be distributed if a non-restorative procedure is performed or if the patient has a permanent or temporary stoma. Surgeons are requested to ask specific questions regarding the evaluation of urinary and sexual dysfunction during follow-up appointments at 6 months and 12 months postoperatively (online supplemental file E).

**Table 1 T1:** Study schedule

Study schedule	Before (C)RT	After (C)RT	6 month-PO	12 month-PO	24 month-PO	36 month-PO
**Questionnaires**	X		X	X		X
**Pelvic MRI**	X	X*			X*	

* Not required.

(C)RT(chemo)radiotherapyPOpostoperative

### Statistics

Analyses will be conducted in Statistical Package for the Social Sciences (SPSS, Chicago, Illinois). LR and LLR will be compared with a percentage of 13% obtained from the two historic cohorts (Consortium and Snapshot) using a one-sample z-test. Baseline characteristics will be described using numbers and proportions for categorical variables; for continuous data, means with 95% CIs or medians with IQR will be used according to the distribution of the data. Clinical data will be described including the type of neoadjuvant treatment, resection margin, height of the tumour, tumour stage (cT/cN stage) and threatened mesorectal fascia (≤1 mm distance). For functional outcomes, descriptive statistics will be used, while quality of life will be analysed using repeated measure analyses. To compare subgroups within the LaNoReC study, χ^2^ tests and Fisher’s exact tests will be performed for categorical variables. Differences in continuous variables will be analysed using student’s t-tests or Mann-Whitney U tests, according to the distribution of the data. A p value of ≤0.05 will be considered statistically significant.

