**Methods and analysis:**

A prospective registration study will be opened in hospitals in which the involved multidisciplinary team members (radiologists, radiation oncologists, surgeons and pathologists) have received dedicated training to enhance knowledge and awareness of LLNs and in which standardised treatment including LLND has been implemented. Patients with rectal cancer and at least one enlarged LLN (short-axis ≥7.0 mm), or intermediate LLN (short-axis 5.0–6.9 mm) with at least one malignant feature on primary MRI, evaluated by a trained radiologist, are eligible. Patients will undergo neoadjuvant treatment by trained radiation oncologists, followed by TME surgery in combination with a minimally invasive, nerve-sparing LLND performed by trained surgeons. LLND specimens are evaluated by trained pathologists or grossing assistants. The primary outcome is LLR rate 3 years postoperatively. Secondary outcomes are morbidity, disease-free survival, overall survival and quality of life. To demonstrate a significant reduction in LLR rate from 13% (based on historical control data) to 6% after optimised treatment, 200 patients with enlarged LLNs are required.

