## Introduction

 The last few decades have witnessed major improvements in rectal cancer treatment due to the use of MRI for adequate staging, neoadjuvant treatment and the total mesorectal excision (TME) procedure, as reflected by a decrease in the overall local recurrence (LR) rate to 5%–10%.^1^,^3^ Consequently, occurrence of LRs has shifted from a central location to the lateral pelvic compartments, the latter now comprising approximately half of all LRs.^4^ Most likely, these are caused by lymphatic spread to lateral lymph nodes (LLNs) in locally advanced rectal cancer (LARC) in the lower part of the rectum.^4^ When these LLNs are primarily enlarged (short-axis ≥7.0 mm), the percentage of lateral LR (LLR) has been reported to be up to 20% after 5 years following neoadjuvant (chemo)radiotherapy (C)RT and TME.^5^,^7^ LLRs are associated with fewer complete resections, and consequently, poorer survival outcomes compared with recurrences at other sites.^8 9^

Different approaches are used worldwide to treat enlarged LLNs. Eastern surgeons, particularly from Japan, perform an LLN dissection (LLND) to decrease the risk of LLR,^10^ despite the associated morbidity.^11 12^ However, the generalisability of studies supporting LLND’s effectiveness is limited due to exclusions of patients with LLNs ≥10.0 mm and the differences in population and practice between the East and the West.^13^ In the West, physicians primarily rely on neoadjuvant (C)RT to treat enlarged LLNs, or they are erroneously considered as systemic disease, leading to undertreatment resulting in high LLR rates.^11^

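### Overall local recurrence is to be tested against 13%, which is the historical lateral recurrence rate, so this supporting comparison has no benchmark of its own and can mislead

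*Protocol article*

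**What the plan says.** The Statistics section gives one null value for two endpoints: "LR and LLR will be compared with a percentage of 13% obtained from the two historic cohorts (Consortium and Snapshot) using a one-sample z-test".

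The Sample size section says what that value is: "The sample size is based on a historical control group with an average 3-year LLR rate of 13% (11% Snapshot and 16% Consortium"). It also gives the population and treatment behind it: "in low LARC with LLNs ≥7.0 mm after (C)RT+TME (without LLND"). The abstract uses the figure in the same sense: "To demonstrate a significant reduction in LLR rate from 13% (based on historical control data) to 6% after optimised treatment". The Discussion likewise attaches the fall from 13% to 6% to LLR only.

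The Introduction uses LR for overall local recurrence and treats lateral recurrences as one part of it, "the latter now comprising approximately half of all LRs".

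The abstract names 3-year LLR as the primary outcome. LR does not appear among the secondary outcomes in the abstract or among the main secondary objectives in the Objectives section.

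**The concern.** LR and LLR are nested: every lateral recurrence is a local recurrence, but not the reverse. A single historical percentage can be the right null for both only if the historical patients had no non-lateral recurrence at all. If they had some, 13% is too low a null for LR.

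A null that is too low has two effects on the LR result. A real fall in LR may be reported as no difference, and an LR rate that has not changed, or has even fallen, may be reported as a significant increase. Either result would sit awkwardly beside a positive LLR result and blur the study's main message, although the cause would be the benchmark and not the treatment.

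**Working it through.** **Inputs from the protocol article.** Null 0.13, alternative 0.06, n = 190, two-sided 5%, 90% power, 5% drop-out (Sample size); one-sample z-test (Statistics).

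**Input not in the article.** The historical 3-year LR rate for nodes ≥7.0 mm after (C)RT+TME without LLND. I write it as 13% + q, where q is the non-lateral recurrence rate in percentage points, and vary q from 0 to 13. The upper end is what follows if the Introduction's share of about one half is applied to this group: 13 / 0.5 = 26, so q = 26 − 13 = 13. That share describes rectal cancer in general, so q = 13 marks the end of a range and is not an estimate.

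**Step 1. Reproduce the plan's own figure (LLR).**

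n = [z₀.₉₇₅·√(p₀(1−p₀)) + z₀.₉₀·√(p₁(1−p₁))]² / (p₀−p₁)²

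= [1.960·√(0.13×0.87) + 1.282·√(0.06×0.94)]² / 0.07²

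= [0.659 + 0.304]² / 0.0049 = 189.45, rounded up to 190.

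Power at 190 is 90.1% by the normal approximation and 89% by exact binomial calculation. 190 / 0.95 = 200. Both stated figures reproduce, and they concern LLR only.

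**Step 2. Cut-offs of the test against 13%.** The standard error under the null is √(0.13×0.87/190) = 0.0244. The test shows a reduction at 15 or fewer events of 190 (z = −2.09; 16 events give −1.88) and an increase at 34 or more (z = 2.01; 33 events give 1.79).

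**Step 3. Apply these cut-offs to LR.** Assume that LLR falls from 13% to 6% and that q is the same historically and in the study. LR then falls from 13 + q to 6 + q, always by 7 points. Exact binomial probabilities at n = 190 are P(X ≤ 15) for a fall and P(X ≥ 34) for an increase. The matched column repeats the test with 13% + q as the null.

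| q | True LR, historical → study | Shows fall, against 13% | Shows fall, against 13% + q | Shows increase, against 13% |
|---|---|---|---|---|
| 0 | 13% → 6% | 89% | 89% | 0% |
| 1 | 14% → 7% | 74% | 88% | 0% |
| 3 | 16% → 9% | 35% | 81% | 0% |
| 5 | 18% → 11% | 10% | 73% | 0.3% |
| 7 | 20% → 13% | 2% | 73% | 3% |
| 13 | 26% → 19% | about 0% | 61% | 68% |

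**Step 4. LR unchanged.** If the study's LR rate equals the historical 13% + q, the test against 13% shows a false increase with probability 27% at q = 3, 54% at q = 5 and over 99% at q = 13. The chance of a false reduction is 1.9% at q = 0 and shrinks as q grows (0.7% at q = 1, 0.1% at q = 3). The bias therefore runs in one direction only.

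**The case against.** The strongest reply is that the consequences are limited. LR is neither the primary outcome nor a listed secondary one. The hypothesis and the sample size concern LLR, and the interim analysis singles out LLR among the oncological outcomes. The LLR test uses the rate that belongs to it. All of this stands and sets the severity.

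A second reply is that the sentence may be loose drafting in a condensed article. That is possible. But the article itself fixes the test, the null and both endpoints, and no other section corrects it, so this is a misstatement and not a detail left to a fuller document.

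A third reply is that the Introduction gives overall LR as 5%–10%, so 13% might look generous for LR. That figure describes rectal cancer in general. The study's benchmark group has nodes ≥7.0 mm, and its lateral rate alone is 13%.

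A reader might also infer that the LR test is bound to give a wrong answer, or that a particular loss of power can be stated. The documents do not support either. They give no historical LR rate for this group, and strictly they establish only that the rate is not below 13%. If non-lateral recurrence were rare, the error would be small. Applying the one-half share to the general 5%–10% gives q of 2.5 to 5; applying it to 13% gives q = 13. Neither is a reliable value for this population, so only the whole range can be shown.

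**Conclusion.** The point holds as a moderate correction to a supporting comparison. The LR null is wrong as written, because 13% is defined in the article as a lateral rate and LR is the wider endpoint. The direction of the error is known: it works against showing a benefit. It can hide a real fall in LR or produce a false increase, but it does not create a false benefit.

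The size is not known. It runs from nil at q = 0 to a probable reversal of the conclusion at q = 13. The figures rest on 190 evaluable patients, a fall in LLR from 13% to 6%, and non-lateral recurrence that is equal in the historical and study patients. The primary LLR test and its sample size of 190, or 200 with drop-out, are untouched.

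**What to change.** In the Statistics section, restrict the one-sample test against 13% to LLR. Report 3-year LR as an estimate with a 95% confidence interval and no test against 13%.

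Test LR only if a 3-year LR rate is available for the same historical groups (nodes ≥7.0 mm, (C)RT+TME without LLND), and then state that rate and its source as a separate benchmark. The article does not say whether both cohorts can supply it, so the confidence interval should be the default.

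The default costs one sentence, with no additional patients or data and no change to the primary analysis. The optional LR test also requires obtaining the historical LR rate.
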